To investigate the clinical outcome rates (including all-cause mortality, ischemic stroke/transient ischemic attack/systemic embolism, intracranial hemorrhage, and major bleeding) in atrial fibrillation patients
To develop predictive model for clinical outcomes
Secondary objectives
To investigate the factors predicting clinical outcomes in patients with atrial fibrillation;
To study the clinical outcome rates (including all-cause mortality, ischemic stroke/transient ischemic attack/systemic embolism, intracranial hemorrhage, and major bleeding) in atrial fibrillation patients stratified by different types of antithrombotic medications, including warfarin, stratified by TTR, the 4 types of DOACs, stratified by dosage, and antiplatelet agents;
To validate data from COOL-AF Phase 1, such as the COOL-AF predictive models for all-cause mortality, ischemic stroke/systemic embolism, and major bleeding; and
To conduct an economic analysis of the complications related to ischemic stroke and the cost-effectiveness of stroke prevention and treatment in atrial fibrillation patients.

COOL-AF = COhort of antithrOmbotic use and cLinical outcomes in patients with Atrial Fibrillation; DOAC = direct oral anticoagulant; TTR = time in therapeutic range.

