### Data collection

The following data were collected at the baseline visit:•Demographics (age, sex, weight, height)•Type of AF (new, paroxysmal, persistent, permanent)•Symptoms of AF (dyspnea, palpitations, dizziness, chest pain, syncope, fatigue, and the European Heart Rhythm Association score)•Duration of AF•Method of AF diagnosis•Medical history (history of stroke/transient ischemic attack [TIA], carotid surgery/stenting, percutaneous coronary intervention, coronary artery bypass surgery, myocardial infarction, peripheral arterial disease, bleeding history, heart failure)•Cardiovascular risk factors (hypertension, type 2 diabetes (T2D), smoking, dyslipidemia]•AF management (rate control, rhythm control, cardioversion, ablation)•Anticoagulant/antiplatelet therapy•Vital signs (blood pressure, heart rate)•INR values and dates•Other laboratory values•Cardiac imaging results•Components of the CHA_2_DS_2-_VASc score•Components of the HAS-BLED score•Components of the SAMe-TT2R2 score•EQ-5D-5L

Because antithrombotic pattern is one of the main interests of this registry, the data collection on the antithrombotic agents included the types and doses of OAC and antiplatelets. Anticoagulants are vitamin K antagonist (warfarin), and DOACs (dabigatran, rivaroxaban, apixaban, and edoxaban). Doses of DOACs are recorded as follows: dabigatran 110 and 150 mg twice daily, rivaroxaban 10, 15, or 20 mg once daily, apixaban 2.5 or 5 mg bid, and edoxaban 15, 30, or 60 mg od. Antiplatelets are aspirin and P2Y12 inhibitors (clopidogrel, prasugrel, and ticagrelor). Doses of aspirin are recorded. Combination of OAC and antiplatelet is also recorded. Data collection at the follow-up visit was similar to that at the baseline visit with the addition of clinical events and data related to that event. The source document of the clinical outcomes was required to be uploaded into the web system.

Schedule of study procedures at baseline and follow-up is shown in Table 3. Summary of study protocol and design of the COOL-AF Phase 2 study is shown in the Central Illustration.

**Table 3 tbl3:** Schedule of Study Procedures

	Initial Visit	Data Collection Interval					
		6 mo	12 mo	18 mo	24 mo	30 mo	36 mo
Assessments (prescreen)							
Informed consent	√						
Inclusion/exclusion criteria	√						
Demographics	√						
Diagnosis	√						
Symptoms of AF	√	√	√	√	√	√	√
Cardiovascular history	√						
Additional medical history	√						
Bleeding history and risk factors for bleeding							

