Vital signs	√	√	√	√	√	√	√
Investigations							
Laboratory INR values	√	√	√	√	√	√	√
Other laboratory findings	√	√	√	√	√	√	√
Cardiac imaging	√	√	√	√	√	√	√
AF treatment							
Nonmedication treatment	√	√	√	√	√	√	√
Rate and rhythm control medication	√	√	√	√	√	√	√
Antithrombotic therapies	√	√	√	√	√	√	√
Other medications	√	√	√	√	√	√	√
Components of CHA_2_DS_2_-VASc score	√	√	√	√	√	√	√
Components of HAS-BLED score	√	√	√	√	√	√	√
Components of SAMe-TT2R2 score	√	√	√	√	√	√	√
Outcomes		√	√	√	√	√	√
Quality of life (QOL) questionnaires							
EQ5D-5L	√				√		√

AF = atrial fibrillation, INR = international normalized ratio.

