#### Model validation

Model applicability assessment will be performed according to the Prediction model Risk Of Bias ASsessment Tool suggestions.^24^ Bootstrapping based on 100 to 1,000 bootstrap samples will be used to verify the fitted model. Calibration will be tested using the calibration slope based on the observed and predicted hazards of the outcome.^25^ The Harrell C-statistics will be used to measure model discrimination. C-statistics vary from 0 to 1, and a value close to 1 reflects a good prediction model.^26^ Receiver-operating characteristics curve will be used to calculate the area under curve and to compare C-statistics. The D-statistic assesses the discrimination ability of the fitted model for low- and high-risk patients.^26^ C- and D- statistics will also be calculated after the bootstrapping as an internal validation. The Brier score will be evaluated to assess the predictive ability of the model.^27^ Net reclassification index and integrated discrimination index will be calculated based on previously proposed methods to determine the influence of the predictive model on the reclassification of the study subjects.^28^ Decision-curve analysis will be used to estimate the clinical usefulness of the prediction models by assessing the ability to make better decisions with a model than without it.^29^

All statistics were performed using the SPSS statistical software version 18.0 (SPSS, Inc) and R version 3.6.3 (R Foundation for Statistical Computing).

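### Clinical usefulness is to be read from decision curves against no model, with no existing score named as benchmark for the curve, NRI, IDI or C-statistics

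*Protocol article*

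**What the plan says.** In Model validation, the article assigns the judgment of clinical usefulness to decision-curve analysis, described as "assessing the ability to make better decisions with a model than without it". It names no existing score or model to be drawn on the same axes.

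The same section plans other comparative measures, also without naming a reference:
- The net reclassification index (NRI) and integrated discrimination index (IDI) are to be used "to determine the influence of the predictive model on the reclassification of the study subjects".
- On discrimination: "Receiver-operating characteristics curve will be used to calculate the area under curve and to compare C-statistics".

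Elsewhere the article shows that benchmarks are at hand:
- The baseline list under Data collection includes "Components of the HAS-BLED score", and the corresponding components of CHA2DS2-VASc.
- The schedule in Table 3 has rows for "Components of CHA_2_DS_2_-VASc score" and "Components of HAS-BLED score", both ticked at the initial visit and at all six follow-up visits.
- A secondary objective in Table 1 is to validate Phase 1 results, "such as the COOL-AF predictive models for all-cause mortality, ischemic stroke/systemic embolism, and major bleeding".

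**The concern.** Developing new prediction models is a primary objective, and the expected benefits include Thai guidelines on antithrombotic use. The practical question for a new model is therefore whether it supports better decisions than the tools a Thai clinic could already use. For SSE and major bleeding those are the two scores whose components are recorded here. For all three outcomes they also include the Phase 1 models.

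The usual references on a decision curve are to treat everyone or to treat no one. Net benefit above the better of these contains whatever an existing score would have delivered, plus whatever the new model adds. A curve with only the default references cannot separate the two parts. Near the average risk, a model with modest discrimination will usually lie above both defaults, so that result says little about added value. At stake is how the usefulness of the new models is reported. Their estimation, the data collected and the sample size are not affected.

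**Working it through.** **1. The article's own figure.** The only computable figure nearby is the sample size. Ten events for each of about ten candidate variables is 10 × 10 = 100 events. The stated 3,334 patients for SSE imply a risk of 100/3,334 = 3.0%. Adding 10% gives 3,334 × 1.10 = 3,667.4, which matches the stated 3,667. The point does not depend on this. It only supplies a plausible event risk, since the article does not print the Phase 1 SSE rate.

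**2. Formula.** At risk threshold t and event risk p,

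net benefit = p·TPR − (1 − p)·FPR·t/(1 − t).

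Treat-none has net benefit 0. Treat-all has p − (1 − p)·t/(1 − t). The apparent gain of a model is its net benefit minus the better of these two.

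**3. A case that can be checked by hand.** Take p = t = 0.03, so treat-all and treat-none are both 0. Assume calibrated scores, normally distributed with equal variance in patients with and without events, and separation d = √2·z(C). At t = p the net benefit reduces to p·(TPR − FPR), with TPR = Φ(d/2) and FPR = 1 − Φ(d/2).
- New model, C = 0.70 (assumed): d = 0.742, TPR = 0.645, FPR = 0.355, gain = 0.03 × 0.289 = 8.7 per 1,000.
- Existing score, C = 0.65 (assumed): d = 0.545, TPR = 0.607, FPR = 0.393, gain = 0.03 × 0.215 = 6.4 per 1,000.
- Share already available: 6.44/8.68 = 74%. Increment: 2.2 per 1,000.

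With the same two C-statistics the share is 19% at a 1% threshold, 53% at 2% and 47% at 5%.

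**4. A nested model over a grid.** Let logit risk = a + x + z, with mean risk 3%. Here x is the existing score (SD 0.5 or 0.6) and z is information only the new model has (SD 0.3 or 0.4). The existing score is taken as perfectly recalibrated. These settings give C of about 0.64-0.66 for the existing score and 0.66-0.69 for the new model. Gains are per 1,000 over the better default. Two of the four settings are shown:

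| Existing C / new C | Threshold | Existing gain | New gain | Existing share | Increment |
|---|---|---|---|---|---|
| 0.66 / 0.68 | 3% | 7.0 | 7.8 | 90% | 0.8 |
| 0.66 / 0.68 | 5% | 2.3 | 3.0 | 76% | 0.7 |
| 0.637 / 0.674 | 2% | 1.3 | 2.3 | 57% | 1.0 |
| 0.637 / 0.674 | 5% | 1.4 | 2.7 | 50% | 1.4 |

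Over all four settings at thresholds of 2-5%, the existing score's share is about 50-90% and the increment about 0.5-1.6 per 1,000. At thresholds of 1-1.5% the share falls to about 21-70%.

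**5. Sensitivity to the assumptions.** With the method of step 3 and wider inputs (existing C 0.60-0.65, new C 0.65-0.75, thresholds 1-5%), the share runs from about 0% (C 0.60 against 0.70 at 1%) to 100% (equal C). The mechanism is certain, but its size depends on figures that the article does not give. Only an SSE-like risk was examined; nothing was computed for bleeding or death.

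**The case against.** The strongest reply is that the quoted clause is a one-line description of what decision-curve analysis does, placed among similar glosses on other statistics. It does not mention treat-all or treat-none, and it does not exclude further curves on the same plot. Which models are overlaid is a detail that a journal article may leave to the full protocol or analysis plan. NRI and IDI cannot be calculated without a reference model, C-statistics are to be compared, and the Phase 1 models are to be validated in this cohort. Some assessment of incremental value is therefore implied.

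Much of this stands. A reader might infer that the plan will credit the usefulness of existing scores to the new models, or will declare the new models superior. The documents do not support that. They set no criterion for usefulness, no threshold range and no claim of superiority, and the other planned measures imply some comparator.

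What the reply does not remove is that no model is the only reference stated for the usefulness claim, while every other comparison in the section lacks a named reference. NRI, IDI and C-statistics do not measure net benefit, so they cannot stand in for a benchmark curve. Nor do the two clinical scores serve every outcome: the article gives neither a benchmark role for all-cause death, where the Phase 1 model is the natural comparator.

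**Conclusion.** The point holds in a limited form. As written, the decision-curve analysis can show that a new model is better than no model. It cannot show that the model is better than CHA2DS2-VASc, HAS-BLED or the Phase 1 models, and no benchmark is named for the other comparative measures. Existing usefulness can therefore be credited to the new models; the article does not show that it will be.

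The illustrative size is a 50-90% share for the existing score and an increment of 0.5-1.6 per 1,000. It rests on a 3% SSE risk inferred from the sample size, assumed C-statistics, a perfectly recalibrated existing score and thresholds of 2-5%. It should not be quoted as a property of this registry, where the size is unknown. The point is worth correcting before results are seen, because a benchmark chosen afterwards could be a flattering one.

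**What to change.** In Model validation:
- Add net-benefit curves for CHA2DS2-VASc (SSE), HAS-BLED (major bleeding) and the corresponding Phase 1 model (death, SSE and major bleeding). Recalibrate each to the Phase 2 cohort, and keep treat-all and treat-none for reference.
- Name the same comparators for NRI, IDI and the comparison of C-statistics.
- Base any claim of added usefulness on the optimism-corrected difference in net benefit between the new model and the existing comparator, with a bootstrap interval.

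The cost is small. The score components are already scheduled, validation of the Phase 1 models is already an objective, and bootstrapping is already planned. Sample size and data collection do not change. The downside is a little more analysis and reported usefulness that may look smaller.

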### Sample size calculation

The sample size calculation for the predictive model development was based on the 10 events per variable concept, which suggested that we need at least 10 events per candidate variable.^30^ The results from COOL-AF phase 1 indicated that the number of candidate variables for death, SSE, and major bleeding is approximately 10. Using the rate of death, SSE, and major bleeding from COOL-AF phase 1,^3^ the number of patients needed for predictive model development was highest at 3,334 for SSE. If the rate of incomplete or loss follow-up is 10%, the sample size needed was 3,667. This sample size also covers the sample size needed to determine the rate of clinical outcomes (death, SSE, and major bleeding).

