**Methods:**

The COOL-AF Phase 2 study is a prospective observational multicenter study of patients with known or newly diagnosed nonvalvular AF in Thailand. The aim is to achieve a sample size of 3,667 patients from 33 centers. Patients will be followed up every 6 months for up to 3 years. Data collection on and doses of oral anticoagulants (warfarin, dabigatran, rivaroxaban, apixaban, and edoxaban) and antiplatelets are collected. The study outcomes include death, ischemic stroke/systemic embolism, major bleeding, myocardial infarction, heart failure, and quality of life. All events will be adjudicated.

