**Results:**

Enrollment started in June 2024. The results of the COOL-AF phase 2 registry will be reported when enrollment is complete and one year of follow-up data is available.

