### Trial status

The research funding for the COOL-AF Phase 2 study was approved by the Health System Research Institute and the Heart Association of Thailand. The study protocol was approved by the CREC (COA-CREC103/2023). The local Institutional Review Board has approved the study at one-half of the sites. The web-based system is in the final stage of preparation. The enrollment began in June 2024. Last patient recruitment is expected in June 2026, and the last follow-up visit is expected to be in June 2029.

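### The 10% loss allowance is added to 3,334 rather than divided out: 3,667 covers 9.1% complete loss, not 10% (a minor correction)

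*Protocol article*

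**What the plan says.** The Sample size calculation section of the protocol article uses the events-per-variable rule: "we need at least 10 events per candidate variable". It takes the number of candidates from phase 1: "the number of candidate variables for death, SSE, and major bleeding is approximately 10". The event rates also come from phase 1 and are cited without figures.

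Of the three outcomes, SSE drives the size: "the number of patients needed for predictive model development was highest at 3,334 for SSE". The final step is the allowance for loss: "If the rate of incomplete or loss follow-up is 10%, the sample size needed was 3,667".

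The resulting 3,667 is repeated as the study target in the Abstract, under Study design, in the Central Illustration and in Table 6.

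**The concern.** An allowance for loss should ensure that the required number remains after the loss has occurred. The assumed percentage applies to the patients enrolled, so the required number must be divided by the fraction retained. Adding 10% of the required number always gives too few, because the later 10% loss is taken from a larger base.

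The 3,334 appears to carry no margin: it is the number that yields 100 events for 10 candidate variables. SSE is also the outcome with the largest requirement, so the surplus for death and major bleeding does not help it. Taken literally, the stated size therefore ends just under the minimum that the article sets for its most demanding model. Model development is one of the primary objectives.

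**Working it through.** **Inputs, all from the Sample size calculation section**

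- Events per candidate variable (EPV): at least 10
- Candidate variables: approximately 10
- Patients required for the SSE model before loss: 3,334
- Incomplete or lost follow-up: 10%
- SSE proportion: not given as a number, so it is back-calculated below

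**Step 1. Reproduce 3,334**

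Events required = 10 × 10 = 100. Implied SSE proportion = 100 / 3,334 = 0.029994, or 3.0%. In the other direction, 100 / 0.03 = 3,333.3, which rounds up to 3,334. The 3.0% is an inference from the article's figures, but it fits them exactly.

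**Step 2. Reproduce 3,667**

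3,334 × 1.10 = 3,667.4, which rounds to the stated 3,667. This identifies the formula that was used.

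**Step 3. Apply the allowance to those enrolled**

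3,334 / (1 − 0.10) = 3,704.4, which rounds up to 3,705. The difference is 3,705 − 3,667 = 38 patients, and 38 / 3,667 = 1.0%.

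**Step 4. What 3,667 delivers if lost patients contribute nothing**

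- Patients remaining: 3,667 × 0.90 = 3,300.3, about 34 fewer than 3,334
- SSE events: 3,300.3 × 0.029994 = 98.99, about 99
- EPV: 99 / 10 = 9.9
- Largest complete loss that still leaves 3,334: 1 − 3,334 / 3,667 = 9.08%, or 9.1%

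**Step 5. Sensitivity to partial follow-up**

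Suppose the 10% who are lost (366.7 patients) contribute on average a fraction x of full follow-up, with a roughly constant hazard. The effective number is then 3,300.3 + 366.7x. Setting this equal to 3,334 gives x = 33.7 / 366.7 = 0.092, which is about 3.3 of 36 months. At x = 0.5 the effective number is 3,300.3 + 183.4 = 3,483.7, about 3,484 and above the requirement.

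**The case against.** The strongest reply is that the slip has almost no practical consequence, and most of that reply stands.

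- The shortfall is one event in 100, while the candidate count is itself only approximate. One more candidate would raise the requirement by 10 events, ten times the shortfall.
- The planned model is a Cox model with six-monthly data collection, so patients who leave early contribute time and any events up to censoring. By Step 5, an average of little more than three months of follow-up among the lost patients closes the gap.

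What does not yield is the sentence itself. It says that 3,667 is the size needed under 10% loss, and on its own terms that is not the result.

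A reader might go further. The Abstract says that results "will be reported when enrollment is complete and one year of follow-up data is available", and one could infer that the SSE model will be fitted at that point with far fewer than 10 EPV. The documents do not support this. They do not say that the prediction model belongs to that report, and follow-up is planned to 36 months, with the last visit expected in June 2029. Neither the SSE rate nor the period it covers is stated, and a condensed article may leave both to the full protocol. If the implied 3.0% were annual, one year of follow-up per patient would already give about 10 EPV (99 events from 3,300 patients).

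**Conclusion.** The point holds as a minor arithmetic error. The 10% allowance was applied as a multiplier of 1.10 instead of a division by 0.90, so the stated 3,667 should have been 3,705 or should have been described as allowing for 9.1% loss.

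The EPV of 9.9 is the worst case. It rests on the back-calculated 3.0%, on exactly 10 candidate variables, and on lost patients contributing no usable follow-up. If they contribute even modest follow-up, the criterion of 10 is met, so it would be too strong to say that the study misses its own requirement. The multiplication itself is certain. The finding does not threaten the design, and it says nothing about when the model will be fitted.

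**What to change.** Correct the sentence and keep the enrolment target. Suitable wording would be: *A sample of 3,667 allows for 9.1% loss to follow-up; with 10% complete loss it gives about 3,300 evaluable patients, about 99 SSE events and 9.9 events per candidate variable.* The sponsor could add that patients with partial follow-up contribute to the Cox model until censoring, so the effective number is expected to be higher.

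The cost is one reworded sentence with a slightly less favourable figure. No patients are added and no analysis changes.

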### Expected benefits

1.To ascertain the current usage patterns of antithrombotic medications in AF patients, particularly whether the use of DOACs has increased since the COOL-AF Phase 1 study and whether there have been improvements in the appropriate use of warfarin regarding INR levels and TTR.2.To establish Thai guidelines for the appropriate antithrombotic medication use in AF management, aiming to enhance the quality and standardization of care.3.To assess the rates of ischemic stroke and major bleeding in Thai populations with AF who are receiving warfarin and DOACs.4.To foster a culture of collaboration and serve as a foundation for future joint research projects among institutions, hospitals, and cardiology societies.5.To understand the economic implications of using DOACs in AF patients.6.To advance the care of AF patients by reducing complications such as ischemic stroke and abnormal bleeding, with the goal of alleviating the economic burden associated with this disease.

### Trial status

The research funding for the COOL-AF Phase 2 study was approved by the Health System Research Institute and the Heart Association of Thailand. The study protocol was approved by the CREC (COA-CREC103/2023). The local Institutional Review Board has approved the study at one-half of the sites. The web-based system is in the final stage of preparation. The enrollment began in June 2024. Last patient recruitment is expected in June 2026, and the last follow-up visit is expected to be in June 2029.

